### Small Steps for Big Changes Objectives

The objectives of this randomized controlled trial are to:

Compare differences in cardiorespiratory fitness between HIIT and MICT at 6 and 12 months after the intervention.Examine accelerometry-measured purposeful moderate-to-vigorous physical activity in bouts of ≥10 minutes (MVPA10+) and total accelerometer counts throughout the follow-up year (ie, 3, 6, 9, and 12 months) after the HIIT and MICT intervention. Self-reported adherence to HIIT and MICT exercise prescriptions will be collected at 3-, 6-, 9-, and 12-month follow-up.Examine the following psychological outcomes to explore their potential relationship with free-living adherence: task self-efficacy, self-regulatory efficacy, concurrent self-regulatory efficacy, self-monitoring, outcome expectations, exercise enjoyment, and instrumental and affective attitudes. In addition, differences in acute affect, in-task enjoyment, and perceived exertion between HIIT and MICT will be compared.Examine differences in cardiometabolic health markers. Glucose control and insulin sensitivity will be assessed at baseline, post intervention, and at 6- and 12-month follow-up. Body composition will be assessed at baseline, post intervention, and at 12-month follow-up. Differences in average blood glucose levels between conditions will be examined immediately after the intervention in a subsample of participants.

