#### Proposed Data Analyses

Preliminary analyses will be conducted to test for univariate and multivariate outliers and to test for normality. Data transformations will be conducted if required. Variance between the conditions in baseline outcome variables will be examined. Data will be analyzed on an intention-to-treat basis, with individuals retained within their randomized groups regardless of participation. All significance tests will be assessed at a 5% level of significance and effect sizes will be reported. Sensitivity analysis will be conducted to examine the impact of missing data. We will account for missing data by performing multiple imputation by chained equations to determine whether the results are impacted [74].

Mixed-effects regression with baseline as a covariate and 6- and 12-month outcomes as dependent variables will be used to examine differences in cardiorespiratory fitness between HIIT and MICT. Physical activity behavior assessed by accelerometer will be analyzed similarly but will include 3-, 6-, 9-, and 12-month time points. Mixed-effects regression using baseline and all other time points will be used to determine whether the treatments result in a significant change from baseline.

The mediating effects of task self-efficacy, self-regulatory efficacy, concurrent self-regulatory efficacy, outcome expectations, and self-monitoring will be examined using the INDIRECT macro developed by Preacher and Hayes [75]. The macro computes the following steps simultaneously: (1) regression coefficients for the impact of the intervention on the potential mediators; (2) the association between changes in the mediators and changes in the outcome variable; and (3) the total effects, direct effect, and indirect intervention effects. Bias-corrected bootstrapped 95% asymmetrical CIs will be computed for the indirect effect. Significant mediation will be established if the CIs do not include zero. Multiple mediation models will be computed for MVPA at 12-month follow-up and cardiorespiratory fitness at 12-month follow-up.

A series of mixed-effects regressions will be conducted to examine changes over time between groups in anthropometrics, body composition, biochemical markers, CGM, and additional psychological constructs.

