## Discussion

The *Small Steps for Big Changes* program will be the first randomized trial to examine the efficacy of low-volume HIIT compared with traditionally prescribed MICT as a means of increasing long-term physical activity behavior in individuals at elevated risk of T2D. The impact of HIIT on cardiorespiratory fitness, physical activity adherence, and psychosocial outcomes will be directly compared with current exercise recommendations for this population (ie, moderate-intensity continuous exercise).

The authors acknowledge potential limitations in the proposed methodology. Specifically, exercise studies suffer from potential selection bias, which could impact the generalizability of the results. Furthermore, the considerable number of outcome measures may limit an individual’s willingness to participate. However, the number of outcome measures included in this study is similar to other exercise randomized controlled trials [76,77]. Generalizability of the findings may also be limited because of the study being conducted on a university campus, which may not reflect the environment of most individuals.

However, the findings from this study have the potential to make substantive contributions to understanding how different types of exercise protocol are tolerated and adhered to and the comparative health outcomes associated with these protocols. These findings could have significant implications for exercise recommendations provided for individuals at risk of diabetes.

In addition, this trial examines the effectiveness of a brief behavioral intervention designed to support the promotion of independent physical activity behavior through facilitation of self-regulatory strategies and efficacy beliefs. This intervention brings together theory and evidence in a carefully constructed intervention that will have the opportunity to examine the causal pathways from cognitions to exercise adherence. Together, the results of this trial have the potential to impact future public health campaigns designed to increase physical activity with individuals at risk of T2D.

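### The mediation rule treats any unadjusted bias-corrected 95% interval that excludes zero as established mediation, on the natural reading for ten indirect effects, although the objective is worded as exploratory

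*Protocol article*

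**What the plan says.** All of the following is in the Protocol article.

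- **Mediators** (Proposed Data Analyses): "The mediating effects of task self-efficacy, self-regulatory efficacy, concurrent self-regulatory efficacy, outcome expectations, and self-monitoring will be examined using the INDIRECT macro". That is five constructs.
- **Outcomes** (same section): "Multiple mediation models will be computed for MVPA at 12-month follow-up and cardiorespiratory fitness at 12-month follow-up". That is two outcomes.
- **Interval** (same section): "Bias-corrected bootstrapped 95% asymmetrical CIs will be computed for the indirect effect".
- **Decision rule** (same section): "Significant mediation will be established if the CIs do not include zero".
- **Level** (same section): "All significance tests will be assessed at a 5% level of significance and effect sizes will be reported". No familywise level is stated for the mediation results.
- **Status of the aim** (Small Steps for Big Changes Objectives): "Examine the following psychological outcomes to explore their potential relationship with free-living adherence".
- **Intended use** (Discussion): the trial "will have the opportunity to examine the causal pathways from cognitions to exercise adherence".

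**The concern.** The objection is to a rule that the article states, not to a detail left for an unseen analysis plan. Each specific indirect effect has its own 95% interval, and a single one that excludes zero is enough to call mediation established. That is the language of a confirmed finding, set against an objective that only explores.

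The null that matters is realistic here. An indirect effect of HIIT versus MICT is zero when the arms do not differ on the mediator. Study Design says both arms get the same counselling, and Exercise Counseling shows that the counselling is what targets these cognitions. The Introduction argues that self-efficacy predicts activity. No arm difference combined with a real mediator–outcome association is the setting in which such a rule produces more false positives. At stake is a chance result reported as the mechanism by which one exercise format works better than the other.

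**Working it through.** **1. Analysable numbers.** The article's 41 per group reproduces: n = 2 × (1.96 + 0.84)² × 16² / 10² ≈ 40.2, rounded up to 41, or 82 in total. With 100 randomised and about 20% loss, 100 × 0.80 = 80 complete.

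**2. Number of effects.** 5 mediators × 2 outcomes = 10. Table 2 scores outcome expectations on separate likelihood and value scales, so the count could be higher. If the rule is meant for the total indirect effect only, there are 2.

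**3. Reference bounds.** For independent tests at exactly 5%: 1 − 0.95⁵ = 22.6% and 1 − 0.95¹⁰ = 40.1%. Neither describes this plan. Mediators and outcomes are correlated, the two outcomes share the same arm-to-mediator paths, and the test of a product of paths is often conservative.

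**4. Simulation.** Two arms, no arm effect on any mediator (every indirect effect is truly zero), five mediators in one model per outcome, two outcomes with residual correlation 0.3, 1000 bootstrap samples, 2000 trials per row. The mediator correlation ρ and the slope b (per residual SD, equal for all mediators and both outcomes) are assumptions, because the article gives neither. The variance explained is R² = V/(1 + V), with V = b² × (5 + 20ρ). For example, b = 0.15 and ρ = 0.3 give V = 0.0225 × 11 = 0.2475 and R² = 20%.

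Chance that at least one of ten bias-corrected 95% intervals excludes zero:

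| b | ρ | R² | n = 82 | n = 100 |
|---|---|---|---|---|
| 0 | 0.3 / 0.5 / 0.7 | 0% | 5.6 / 6.2 / 5.0% | 6.7 / 5.9 / 4.9% |
| 0.15 | 0.3 / 0.5 / 0.7 | 20 / 25 / 30% | 16.3 / 13.6 / 10.1% | 17.6 / 14.2 / 8.6% |
| 0.3 | 0.3 / 0.5 / 0.7 | 50 / 57 / 63% | 29.5 / 24.6 / 18.0% | 31.1 / 28.2 / 17.5% |
| 0.5 | 0.3 / 0.5 / 0.7 | 73 / 79 / 83% | 32.7 / 30.0 / 24.3% | 33.0 / 28.3 / 23.7% |

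**5. Runs set by R²** (n = 80, ρ = 0.3 and 0.5, residual correlation 0.5, 600 trials):

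- 10% in both outcomes: about 9%.
- 20% in both: 10–13%.
- 20% for MVPA and 5% for fitness: 8–14%.
- 30% for MVPA and 10% for fitness: 13–17%.

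The simulation error is about √(0.13 × 0.87 / 600) = 1.4 percentage points. Together with the b = 0.15 rows, and allowing for associations carried by one or two mediators, this gives roughly 9–18% for an R² of 5–30%. The edge is not sharp. At b = 0.2 and ρ = 0.3, where V = 0.04 × 11 = 0.44 and R² = 31% in both outcomes, the rate at n = 80 was 22%.

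**6. Per-test rate.** In the b = 0.15 rows the average per-test rate is 1.2–2.3%, below nominal. It reaches about 8% for a single effect when only one or two mediators carry the association.

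**7. Percentile 95% intervals.** In the b = 0.15 rows the any-of-ten rate falls to 6.4 / 5.5 / 3.9% (n = 82) and 7.3 / 6.1 / 3.2% (n = 100). Over the R² 5–30% scenarios it is about 3–9%, and the worst per-test rate is about 5%.

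**8. Other readings.** If the rule means the total indirect effect on each outcome, the chance of at least one false result is about 4–6%. If each mediator were instead fitted alone, the any-of-ten rate was 25–28%. That is not the natural sense of a multiple mediation model that names five mediators.

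**The case against.** **The aim is exploratory and secondary.** The objective says so, the primary outcome is VO2 peak, and the Discussion speaks of an opportunity to examine pathways without claiming a result. The rule can be read as no more than a definition of statistical significance at the article's 5% per test. This largely stands and sets the weight of the point. It does not remove the mismatch between an exploratory objective and a rule that calls mediation established.

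**The count of ten is one reading.** The interval sentence speaks of the indirect effect in the singular, which could mean the total effect. That cannot be ruled out. Naming five mediators makes ten the more natural reading, and the article should say which is meant.

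**The rate could be made to look much larger.** A reader might infer a false-mediator risk of about 12–36%, or the 40% of ten independent tests. The documents support neither. The top of that range needs slopes of 0.4 for all five mediators on both outcomes, where V = 0.16 × (5 + 20ρ) = 1.76, 2.40 or 3.04 and R² = 64%, 71% or 75%. Nothing in the article suggests that questionnaires explain that much of 12-month accelerometer activity and of VO2 peak, and the self-efficacy literature it cites concerns activity, not fitness.

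**The interval is not generally too liberal.** A reader might infer that the bias-corrected bootstrap exceeds 5% here as a rule. It mostly runs below 5%. The excess is confined to sparse or very strong associations.

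**The null may not hold for every mediator.** Table 2 words task self-efficacy, concurrent self-regulatory efficacy and outcome likelihood by condition, so the arms may truly differ there. The exemplar items for self-regulatory efficacy and self-monitoring are not condition-specific.

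**Conclusion.** The point holds as a minor one. The article fixes an unadjusted rule and wording stronger than its own objective. With no arm difference on the mediators, about 80 completers, all five mediators in one model per outcome and an assumed 5–30% of outcome variance explained, the chance of at least one false mediator is roughly 9–18%. It is about 5–7% if the mediators do not predict the outcomes. Rates in the upper twenties and thirties need well over a third of the variance explained in both outcomes. The slopes and correlations are assumptions, so these are ranges and not estimates for this trial.

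It would be wrong to say that the plan breaches a 5% familywise rate. It promises none, and 5% is its per-test level. No primary or treatment-effect conclusion depends on the mediation results.

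**What to change.** In Proposed Data Analyses:

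1. Replace the bias-corrected interval with a percentile bootstrap 95% interval.
2. State whether the rule concerns the total or the specific indirect effects.
3. Label the specific indirect effects exploratory, in line with the objectives.
4. Replace the sentence that mediation will be established with one that treats an interval excluding zero as hypothesis-generating.

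Making the total indirect effect on MVPA10+ the single deciding test is not needed. It would not answer an objective about individual constructs, and opposing paths can cancel in a total.

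The cost is some power for individual mediators from the percentile interval; the rest is wording and needs no new data. The Results section says that data collection is complete and analysis is underway, so the change should be dated and disclosed. The exploratory label can still be applied in the trial report.

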### Data Management and Quality Assurance

The administrative database (ie, participant information) and questionnaire data will be managed in-house. Random checks will be performed on the entered survey data against paper records. All errors will be logged and corrected. All physiological, anthropometric, and biochemical measures will be conducted in 1 laboratory with established quality assurance systems. All data will be stored in a locked laboratory on password-protected and encrypted computers. Paper records will be stored in a locked filing cabinet.

### Retention

Maximizing retention is an important issue to fully understand exercise adherence rates over the 12-month follow-up. At recruitment, all laboratory visits and community visits will be outlined for the participants and the importance of follow-up testing emphasized regardless of exercise behavior. During the 2-week supervised intervention, participants will book the same appointment time for each day and will be sent all the dates and times by the counselor before day 1 of the intervention. Moreover, 2 of the follow-up appointments will be conducted within the local community at a location and time that suits the participant. It is anticipated that this will help reduce some of the burden on participants in attending a laboratory visit.

### Ethics Approval and Consent to Participate

Ethical approval was provided by the University of British Columbia Clinical Research Ethics committee (H12-02268-A008), with informed consent obtained from all participants in the study.

## Results

The project was funded in 2013 and enrollment began in July 2014. Data collection was complete in March 2017. Data analysis is currently underway, and the first results are expected to be submitted for publication in 2019.

## Discussion

The *Small Steps for Big Changes* program will be the first randomized trial to examine the efficacy of low-volume HIIT compared with traditionally prescribed MICT as a means of increasing long-term physical activity behavior in individuals at elevated risk of T2D. The impact of HIIT on cardiorespiratory fitness, physical activity adherence, and psychosocial outcomes will be directly compared with current exercise recommendations for this population (ie, moderate-intensity continuous exercise).

The authors acknowledge potential limitations in the proposed methodology. Specifically, exercise studies suffer from potential selection bias, which could impact the generalizability of the results. Furthermore, the considerable number of outcome measures may limit an individual’s willingness to participate. However, the number of outcome measures included in this study is similar to other exercise randomized controlled trials [76,77]. Generalizability of the findings may also be limited because of the study being conducted on a university campus, which may not reflect the environment of most individuals.

However, the findings from this study have the potential to make substantive contributions to understanding how different types of exercise protocol are tolerated and adhered to and the comparative health outcomes associated with these protocols. These findings could have significant implications for exercise recommendations provided for individuals at risk of diabetes.

In addition, this trial examines the effectiveness of a brief behavioral intervention designed to support the promotion of independent physical activity behavior through facilitation of self-regulatory strategies and efficacy beliefs. This intervention brings together theory and evidence in a carefully constructed intervention that will have the opportunity to examine the causal pathways from cognitions to exercise adherence. Together, the results of this trial have the potential to impact future public health campaigns designed to increase physical activity with individuals at risk of T2D.

## Appendix

Multimedia Appendix 1 Timeline for Small Steps for Big Changes schedule of enrolment, interventions, and assessments.

Multimedia Appendix 2 Small Steps for Big Changes intervention outline.

Multimedia Appendix 3 Peer-reviewer report from the CIHR.

## Abbreviations

BCT: behavior change technique
BMI: body mass index
CGM: continuous glucose monitoring
DPP: Diabetes Prevention Program
DPPOS: Diabetes Prevention Program Outcome Study
ePARmed-X+: Physical Activity Readiness Medical Examination
HIIT: high-intensity interval training
HR: heart rate
MICT: moderate-intensity continuous training
MVPA: moderate-to-vigorous physical activity
MVPA10+: moderate-to-vigorous physical activity in bouts of ≥10 min
PAR-Q+: Physical Activity Readiness Questionnaire for Everyone
SCT: social cognitive theory
SMS: short message service
T2D: type 2 diabetes
VO_2_peak: peak oxygen uptake
